# Prospective randomized controlled trial to compare laparoscopic distal gastrectomy (D2 lymphadenectomy plus complete mesogastrium excision, D2 + CME) with conventional D2 lymphadenectomy for locally advanced gastric adenocarcinoma: study protocol for a randomized controlled trial

**DOI:** 10.1186/s13063-018-2790-5

**Published:** 2018-08-09

**Keywords:** Gastric cancer, Laparoscopic distal gastrectomy, D2 lymphadenectomy, Complete mesogastrium excision, Randomized controlled trial

## Abstract

**Background:**

Although radical gastrectomy with D2 lymph node dissection has become the standard surgical approach for locally advanced gastric cancer, patients still have a poor prognosis after operation. Previously, we proposed laparoscopic distal gastrectomy (D2 lymphadenectomy plus complete mesogastrium excision [D2 + CME]) as an optimized surgical procedure for locally advanced gastric cancer. By dissection along the boundary of the mesogastrium, D2 + CME resected proximal segments of the dorsal mesogastrium completely with less blood loss, and it improved the short-term surgical outcome. However, the oncologic therapeutic effect of D2 + CME has not yet been confirmed.

**Methods/design:**

A single-center, prospective, parallel-group, randomized controlled trial of laparoscopic distal gastrectomy with D2 + CME versus conventional D2 was conducted for patients with locally advanced gastric cancer at Tongji Hospital, Wuhan, China. In total, 336 patients who met the following eligibly criteria were included and were randomized to receive either the D2 + CME or D2 procedure: (1) pathologically proven adenocarcinoma; (2) 18 to 75 years old; cT2–4, N0–3, M0 at preoperative evaluation; (3) expected curative resection via laparoscopic distal gastrectomy; (4) no history of other cancer, chemotherapy, or radiotherapy; (5) no history of upper abdominal operation; and (6) perioperative American Society of Anesthesiologists class I, II, or III. The primary endpoint is 3 years of disease-free survival. The secondary endpoints are overall survival, recurrence pattern, mortality, morbidity, postoperative recovery course, and other parameters.

**Discussion:**

Previous studies have demonstrated the safety and feasibility of D2 + CME for locally advanced gastric cancer; however, there is still a lack of evidence to support its therapeutic effect. Thus, we performed this randomized trial to investigate whether D2 + CME can improve oncologic outcomes of patients with locally advanced gastric cancer. The findings from this trial may potentially optimize the surgical procedure and may improve the prognosis of patients with locally advanced gastric cancer.

**Trial registration:**

ClinicalTrials.gov, NCT01978444. Registered on October 31, 2013.

**Electronic supplementary material:**

The online version of this article (10.1186/s13063-018-2790-5) contains supplementary material, which is available to authorized users.

## Background

Gastric cancer is the main cause of cancer-related death in the world, especially in East Asia [1]. Although substantial improvements have been achieved in diagnosis and treatment, patients with advanced gastric cancer (AGC) still have a poor prognosis [2]. Surgery is the only curative option for locally advanced gastric cancer. According to the Japanese gastric cancer treatment guidelines [3], gastrectomy with extended (D2) lymphadenectomy is the standard approach in the surgical treatment of gastric cancer. Even so, the recurrence rate of patients with locally advanced gastric cancer who undergo radical operation is still approximately 60% [4].

Dissemination of neoplastic cells has been proven to be the main reason for tumor relapse and cancer-related mortality [5]. To avoid tumor cell spreading or to minimize the residual during operation, *en bloc* resection of the primary lesion and its adjacent tissues, such as the mesentery of the gastrointestinal tract, has begun to be the gold standard of radical surgery [6]. In colon and rectal cancers, complete mesocolic excision and total mesorectal excision have been widely used, and they have improved prognosis significantly [7–11]. However, there is no such operation in the stomach. Conventional D2 lymphadenectomy, which is performed by looking for blood vessels in adipose or connective tissues and by dissecting lymph nodes individually, is still the mainstream surgical procedure for gastric cancer.

Our previous studies have demonstrated the existence of disseminated cancer cells (named metastasis V) in the mesogastrium [12, 13] that presented an understandable mesogastrium model for gastrectomy [14]. Therefore, we put forward D2 lymphadenectomy plus complete mesogastrium excision (D2 + CME) to resect both the primary lesion and adjacent tissue as completely as possible to avoid residual tumor or cancer cell spreading [15]. Although a retrospective study has shown that D2 + CME exhibited advantages in intraoperative hemorrhage and postoperative recovery course [15], there is still no prospective randomized controlled trial assessing its therapeutic effect. To further evaluate the D2 + CME procedure, we initiated this single-center, prospective, randomized controlled trial to compare disease-free survival (DFS), overall survival (OS), recurrence, mortality, morbidity, postoperative recovery course, and other parameters between D2 + CME and the conventional D2 procedure in patients with locally advanced gastric cancer who underwent laparoscopic distal gastrectomy.

### Rationale for the trial

Radical gastrectomy with D2 lymphadenectomy has been the standard surgical procedure for AGC and has significantly improved patient outcome. Even so, patients with locally advanced gastric cancer still have a high recurrence rate and poor prognosis. The main causes of postoperative recurrence might be the minimal residual or potential cancer cell dissemination during operation. Thus, resection of both the primary tumor and the adjacent mesentery as completely as possible to avoid minimal residual or cancer cell spreading should become the optimal surgical procedure.

Previously, we presented the mesogastrium model for gastrectomy and developed an optimal surgical approach, D2 + CME, to achieve a complete excision of the gastric mesentery. In our retrospective study, we demonstrated that this approach showed several advantages in terms of decreasing intraoperative bleeding (12.44 ± 22.89 ml, range 5–100), improving lymph node harvesting (35.04 ± 10.70, range 14–55), and shortening the postoperative recovery course (11.09 ± 4.28 days, range 8–28). However, there is still a lack of evidence derived from a prospective randomized controlled trial. Thus, we conducted this study to evaluate the 3-year DFS, 3-year OS, recurrence, mortality, morbidity, postoperative recovery course, and other outcomes of laparoscopic distal gastrectomy with D2 + CME for locally advanced gastric cancer. In summary, the main purpose of this study is to evaluate the therapeutic results of the D2 + CME procedure and to provide evidence for this optimal surgical approach.

## Methods/design

### Study aims and objectives

The key aim of this study is to assess whether D2 + CME is superior to conventional D2 lymphadenectomy in terms of 3-year DFS. The secondary objectives are to compare D2 + CME with conventional D2 in terms of mortality, morbidity, operative time, intraoperative bleeding mount, harvested lymph node number, compliance rates, and quality of life.

### Trial design

This is a prospective, controlled, randomized single-center trial evaluating the therapeutic effect of laparoscopic distal gastrectomy with D2 + CME versus conventional D2 in 336 patients with gastric cancer. Randomization is at the patient level. Participants are randomized 1:1 to receive either D2 + CME or D2.

This study is designed to evaluate the superiority of D2 + CME compared with D2 alone in terms of DFS. We are supposing differences in 3-year DFS of no less than 15% (60% in D2 vs. 75% in D2 + CME) as demonstrating superiority.

Patients enrolled in this trial are asked to complete at least 3 years of follow-up after operation. Then, with allowance, follow-up will last for 5 years. Follow-up is at 3-month intervals for the first 2 years and at 6-month intervals for the last 3 years. At every follow-up, the patients will undergo a physical examination; their nutritional status will be assessed; and blood tests (including blood count, liver function test, tumor markers) will be performed. Abdominal computed tomography (CT) and endoscopy will be performed twice annually. The date and site of the first recurrence, as well as the date of death, will be recorded. The study flow diagram is shown in Fig. 1, and the Standard Protocol Items: Recommendations for Interventional Trials (SPIRIT) checklist is provided in Additional file 1.

**Fig. 1 Fig1:**
[figure not shown]
Study flow diagram. *AGC* Advanced gastric cancer, *D2* Gastrectomy with D2 lymphadenectomy, *D2 + CME* D2 lymphadenectomy plus complete mesogastrium excision, *LADG* Laparoscopy-assisted distal gastrectomy, *XELOX* Chemotherapy regimen consisting of capecitabine combined with oxaliplatin

### Setting

Participants have been recruited and operated at the Department of Gastrointestinal Surgery, Tongji Hospital, Wuhan, China. There are approximately 350 cases of laparoscopic radical gastrectomy in the hospital per year.

### Study duration

Recruitment for this study began in September 2014 and was completed in June 2018. The 3-year follow-up for all the participants will be completed in the middle of 2021.

### Participants

Patients with AGC who meet the following criteria will be recruited into this study.

#### Inclusion criteria

Aged older than 18 years and younger than 75 yearsBody mass index less than 30 kg/m^2^Primary gastric adenocarcinoma confirmed pathologically by endoscopic biopsycT2–4, N0–3, M0 at preoperative evaluation according to the *AJCC Cancer Staging Manual, Seventh Edition* [16]Expected curative resection via laparoscopic distal gastrectomyEastern Cooperative Oncology Group Performance Status 0 or 1 and American Society of Anesthesiologists (ASA) class I, II, or IIIWritten informed consent

#### Exclusion criteria

Pregnant or breastfeeding womenSevere mental disorderPrevious neoadjuvant chemotherapy or radiotherapyPrevious upper abdominal surgeryOther malignant diseases or combined with another gastric malignant tumor (including lymphoma and gastric stromal tumor)Total gastrectomy

#### Selection of gastrectomy

The selection of gastrectomy is according to the Japanese gastric cancer treatment guidelines (2010 version 3) [3]. Briefly, distal gastrectomy is performed when a satisfactory proximal resection margin (at least 3 cm for T2 or deeper tumors with an expansive growth pattern and 5 cm for those with infiltrative growth pattern) can be obtained. Otherwise, total gastrectomy should be considered. The extent of gastrectomy is evaluated by abdominal CT and laparoscopic exploration. Due to the aim of our research, patients who are not suitable for distal gastrectomy will be excluded.

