### Surgeons and surgical quality control

Surgeons who will participate in this study will meet the following criteria: (1) have performed at least 100 cases of laparoscopic distal gastrectomy with D2 lymphadenectomy and (2) have performed at least 50 gastrectomies annually. These criteria qualified eight surgeons to participate in this study. Among them, seven surgeons who have had no training in the D2 + CME procedure are assigned to the D2 group, and the remaining one, who is the founder of the D2 + CME procedure, performs operations in the D2 + CME group.

Surgical quality control is evaluated by using intraoperative video recordings and the resection margin of the specimens. The extent of gastrectomy and lymph node dissection is based on the Japanese gastric cancer treatment guidelines (2010, version 3) [3]. In the D2 group, the intraoperative videos should clearly show the lymph dissection of stations including 1, 3, 4sb, 4d, 5, 6, 7, 8a, 9, 11p, and 12a. Furthermore, the dissected specimen should be checked by an experienced surgeon or a pathologist to ensure that the proximal resection margin and the removal of lymph nodes are satisfactory (Additional file 2). In the D2 + CME group, under the premise of meeting D2 qualification, the operative procedure should also be under the quality control of CME. Quality control of CME is based mainly on the intraoperative video recordings. In the D2 + CME procedure, the resection of the left and right mesogastria, the left and right gastroepiploic mesogastria, and the posterior mesogastrium should be clearly shown (Fig. 3). Furthermore, a mesenteric scoring system that includes the following parameters is applied for each of mesenteric region: trijunction point exposure (exposure of the incision of the mesentery), mesogastrium body (smooth and shiny surface of mesentery after resection), smooth plane of the surgical bed after mesenteric resection, and high tie ligation of the vessel. According to the quality of surgery, each parameter is scored as 2 (good), 1 (moderate), or 0 (poor) (Additional file 3). Then, the parameter scores are summed to get the mesenteric score. Considering that the posterior mesogastrium is short and often lacks blood supply, we simply score it as 2, 1, or 0. The scores of the operation should be recorded in a formal table (Additional file 4) and analyzed. In a standard D2 + CME surgery, the sum of the mesenteric scores should be at least 30.

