### Randomization, masking, and data collection

All the eligible patients will be registered in this study and randomized to either the D2 + CME group or the D2 group (1:1) on the basis of a computer-generated randomization list (generated using SAS version 9.2 software; SAS Institute, Cary, NC, USA) with a block size of 6. Patient enrollment and randomization will be performed by an independent data collection group (managed by the Department of Epidemiology and Biostatistics, Huazhong University of Science and Technology). The data collection group will then collect patient information and fill out the CRF, including general characteristics, preoperative staging, operative findings, pathological reports, and postoperative outcomes. All the data will be placed into the local database via a data registry server managed by the data collection group. In this trial, the patients and the follow-up staff are masked to the treatment allocation.

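### The exclusion for unsuitability for distal gastrectomy is not confined to findings made before randomisation; if allocation comes first, it can remove randomised patients differently by arm

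*Protocol article*

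**What the plan says.** - **Exclusion rule.** Under Selection of gastrectomy, the protocol article says: "Due to the aim of our research, patients who are not suitable for distal gastrectomy will be excluded". The sentence before it gives the basis for the judgement: "The extent of gastrectomy is evaluated by abdominal CT and laparoscopic exploration". CT is available before surgery; laparoscopic exploration takes place in theatre.
- **Eligibility lists.** The exclusion criteria include an operation, "Total gastrectomy". The inclusion side is worded as an expectation: "expected curative resection via laparoscopic distal gastrectomy" (abstract, repeated in the Inclusion criteria). A patient can therefore meet the expectation before surgery and meet the exclusion once explored.
- **Surgeons.** Surgeons and surgical quality control says that "seven surgeons who have had no training in the D2 + CME procedure are assigned to the D2 group", while the remaining surgeon, "who is the founder of the D2 + CME procedure, performs operations in the D2 + CME group".
- **Randomisation.** Randomization, masking, and data collection says: "All the eligible patients will be registered in this study and randomized to either the" two groups, 1:1 in blocks of 6, by an independent data collection group. Patients and follow-up staff are masked.

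The text does not place randomisation relative to exploration, name who judges suitability, or say how a patient found unsuitable after allocation is counted.

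**The concern.** Each surgeon works in one arm only, so the arm would ordinarily have to be known before the operating surgeon starts. On that order, the rule lets a patient who is already randomised be excluded on a finding made by, or in front of, a surgeon who knows the arm. One surgeon, the originator of the procedure under test, would be applying the criterion in one arm and seven others in the other arm. Their thresholds need not match.

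The criterion is an achievable proximal margin, with a larger margin required for infiltrative growth. It would therefore tend to remove proximal or infiltrative tumours. If those patients do worse, which is an assumption, the arm that excludes more of them looks better on 3-year DFS, and 30-day morbidity could be affected too. Neither safeguard in the text prevents this. Independent randomisation protects the allocation, not retention after it. Masking of patients and follow-up staff does not reach a decision taken in theatre. The bias could run in either direction, because nothing says which arm would exclude more.

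**Working it through.** **1. The plan's own figure.** Inputs from Sample size: 60% v 75%, two-sided 5%, 80% power, z-test. With pooled p = 0.675, n per arm = [1.96·√(2·0.675·0.325) + 0.8416·√(0.60·0.40 + 0.75·0.25)]² / 0.15² = (1.298 + 0.550)² / 0.0225 ≈ 151.9, so 152 per arm and 304 in total. Adding 10% gives 152 × 1.1 = 167.2, so 168 per arm and 336 in total. Both stated figures reproduce. No figure in the plan is wrong on this point.

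**2. What the interim report shows.** Interim analysis gives 165 randomised (82 and 83) and morbidity of 11 of 82 and 15 of 83. The denominators equal the numbers randomised. The split also fits an unbroken list in blocks of 6: 165 = 27 × 6 + 3, so 81 and 81 from full blocks, and the last three divided 1 and 2. No post-randomisation exclusion is visible. That does not rule one out, and it does not set the rule for later patients or for the DFS analysis.

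**3. Illustrative size if exclusion follows allocation.** The documents give neither exclusion rates nor the prognosis of those excluded. Assumptions: no true effect, 3-year DFS of 60% in both arms as randomised, 168 randomised per arm, and DFS of q = 20% to 40% in those excluded.

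DFS among those remaining, with fraction e excluded: (0.60 − e·q)/(1 − e).

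- e = 10%, q = 20%: (0.60 − 0.02)/0.90 = 64.4%
- e = 10%, q = 40%: (0.60 − 0.04)/0.90 = 62.2%
- e = 5%, q = 20%: (0.60 − 0.01)/0.95 = 62.1%
- e = 5%, q = 40%: (0.60 − 0.02)/0.95 = 61.1%

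The type I error uses the plan's two-proportion basis as an approximation to the log-rank test. With d the spurious difference and SE = √[p(1 − p)(1/n₁ + 1/n₂)], it is P(Z > 1.96 − d/SE) + P(Z < −1.96 − d/SE). For 10% v 0% and q = 20%: n₁ = 151.2, n₂ = 168, pooled p = 0.621, SE = 0.0544, d/SE = 0.0444/0.0544 ≈ 0.82, and the two tails sum to 12.9%.

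| Excluded, one arm v the other | Spurious difference (q = 40% to 20%) | Two-sided type I error |
|---|---|---|
| 10% v 0% | 2.2 to 4.4 points | 6.9% to 12.9% |
| 10% v 5% | 1.2 to 2.3 points | 5.5% to 7.1% |
| 5% v 0% | 1.1 to 2.1 points | 5.4% to 6.8% |
| 5% v 5%, same prognosis | 0 | 5.0% |

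The first row is 15% to 30% of the planned 15-point effect (2.2/15 and 4.4/15).

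**4. Equal exclusion.** Losing 10% from both arms leaves 168 × 0.9 = 151.2 per arm and power of about 79.8% for 60% v 75%. That costs a little power and causes no bias if those excluded are alike in both arms.

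**The case against.** The strongest reply is that the order of events is inferred. The exclusion sits among the participant criteria, ahead of the interventions, and it is eligible patients who are randomised. Read in sequence, exclusion comes first. In a single department with an independent group performing the allocation, randomisation after exploration is possible. The rule would then limit generalisability and leave the comparison intact. The flow diagram and the assessment schedule, where the order would normally be shown, are not available here, so their silence cannot be held against the plan. This stands, and it makes the point conditional.

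A reader might go further and infer that arm-specific surgeons are in fact dropping randomised patients in theatre. The documents do not support that. No sentence puts allocation before exploration, none names who decides, and the interim counts show nobody missing.

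A second reply is that analysis sets belong in the statistical analysis plan. That is fair, and the lack of an analysis-set definition is not the point here. The point is a stated exclusion rule, tied partly to an intraoperative finding and not confined to the time before allocation. An analysis plan would have to override that rule.

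Third, the size is conjectural: the prognosis of those excluded is unsourced, and the larger figures need a marked imbalance between arms. This also stands. Finally, the rule concerns only the extent of gastrectomy, so it gives no ground for extending the point to open conversion or to metastatic disease found at exploration.

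**Conclusion.** The concern holds in conditional form. The protocol permits exclusion on a finding made in theatre, has arm-specific surgeons, and does not confine that exclusion to the period before randomisation. If allocation precedes exploration, patients can be removed after randomisation in an arm-dependent way, with possible bias in 3-year DFS and morbidity. If allocation follows exploration, there is no bias from this source.

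On the stated assumptions, the spurious difference runs from zero with equal exclusion of similar patients, through 1.2–2.3 points at 10% v 5%, to 2.2–4.4 points at 10% v 0%. Type I error runs from 5% to about 13%. These are illustrations and do not estimate what happened in this trial. It would be wrong to conclude that the arms have already been unbalanced.

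This is a clarification to settle before the DFS analysis. It becomes an essential correction only if the flow diagram confirms that randomisation precedes exploration.

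**What to change.** 1. State when randomisation takes place relative to laparoscopic exploration.
2. Limit the exclusion in Exclusion criteria and Selection of gastrectomy to findings made before randomisation. This concerns who is counted, not which operation is done.
3. State that the primary DFS analysis includes every randomised patient in the allocated arm, including those found at exploration to need total gastrectomy.
4. Make the distal-gastrectomy-only set a sensitivity analysis.
5. Report any exclusions after randomisation by arm, with reasons.

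The cost is wording, slight dilution of the effect, and follow-up of a few extra patients. Enrolment closed on 28 June 2018, so any patient already dropped may need outcomes collected retrospectively. The primary endpoint is to be evaluated in 2021, which leaves time to settle the rule before that analysis.

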### Interventions

#### Operative approach

Patients in the D2 group receive laparoscopy-assisted distal gastrectomy (LADG) with conventional D2 lymphadenectomy according to the Japanese gastric cancer treatment guidelines (2010, version 3). Operations are performed routinely by experienced surgeons who do not receive training for the D2 + CME procedure. The extent of lymphadenectomy includes Nos. 1, 3, 4sb, 4d, 5, 6, 7, 8a, 9, 11p, and 12a. Dissection of No. 14v is optional, and omentectomy is necessary. Reconstruction is performed in the standard Billroth I/II or Roux-en-Y fashion. The type of reconstruction is determined by the surgeon’s experience (Fig. 2).

